#### Questionnaires

The *IBS-SSS* [16] evaluates the severity of IBS symptoms (score range 0-500) and will be filled in at day -1, day 7, day 14, day 21, day 28, and 3 and 6 months after completion of the intervention. The *GSRS-IBS* [19] evaluates IBS-specific GI symptoms and will be filled in at day -1, day 7, day 14, day 21, day 28, and 3 and 6 months after completion of the intervention. The *BSF* scale [17] will be used as the basis for a stool diary that is filled in during 10 days of screening, during the 28 days of the intervention, and at 3 and 6 months after the intervention. In this diary, the patient will record their stool and stool consistency.

The Hospital Anxiety and Depression Scale [20] will be used to determine the severity of anxiety and depression and will be filled in at days 0 and 29 and 3 and 6 months after the intervention. The Visceral Sensitivity Index [21] measures GI-specific anxiety, that is, anxiety originating from fear of GI symptoms, which is related to the unpredictable symptom pattern commonly found in IBS. The form will be filled in on days 0 and 29, and 3 and 6 months after completion of the intervention.

The Patient Health Questionnaire (PHQ)–15 [22] measures the severity of somatic symptoms. Excluding the 3 GI symptoms in the questionnaire yields a measure of non-GI somatic symptom severity, that is, the PHQ-12 [23]. The form will be filled in at days 0 and 29 and 3 and 6 months after completion of the intervention. The Multidimensional Fatigue Inventory-20 [24] measures general fatigue, physical fatigue, decreased activity, reduced motivation, and mental fatigue. This form will be filled in on days 0 and 29 and 3 and 6 months after completion of the intervention.

The Work Productivity and Activity Impairment Questionnaire–IBS [25] measures whether IBS symptoms affect the ability to work and perform everyday activities with four different variables: absenteeism, presenteeism, overall work impairment, and activity impairment. The form will be filled in on days 0 and 29 and 3 and 6 months after completion of the intervention.

The IBS-QoL [26] is an IBS-specific QoL questionnaire that measures 10 domains that have been found to be relevant to patients with IBS: emotional health, mental health, health belief, sleep, energy, physical functioning, diet, social role, physical role, and sexual relations. The form will be filled in on days 0 and 29 and 3 and 6 months after completion of the intervention.

The Highly Sensitive Person scale [27] is a questionnaire that assesses the degree of environmental sensitivity and personality traits that categorize individuals into low, medium, and highly sensitive persons. The form will be filled in on day 0. The Central Sensitization Inventory [28] focuses on sensitivity to pain and symptoms associated with central sensitization. It comprises 25 health-related symptoms that are common to central sensitization. The form will be filled in on day 0.

The following questionnaires will be web-based: Hospital Anxiety and Depression Scale, Visceral Sensitivity Index, Multidimensional Fatigue Inventory-20, IBS-QoL, PHQ-15, Work Productivity and Activity Impairment Questionnaire–IBS, the Highly Sensitive Person scale, and the Central Sensitization Inventory. The platform on which these questionnaires will be entered provides automated score calculations and, as it will not be possible to skip questions, there will be no missing data. The IBS-SSS, BSF, and GSRS-IBS during the intervention period will be completed using paper questionnaires.

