### Allocation

Patients will be randomly assigned to receive 1 of the 3 treatments in a ratio of 1:1:1. For the allocation of the patients, an external web-randomization software will be used. One of the study dietitians will log into the webpage and enter the initials of the patient, whereby the patient will get assigned to a treatment. No stratification will be made before randomization.

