### Sample Size

The power calculation is based on the primary outcome, where the expected response rate is set to 40% (LCD), 65% (LFTD), and 40% (OMT) in the treatment arms. With 80% power to detect differences between groups, and α=.05, 83 patients will be needed in each group. To account for a 15% dropout rate, we will assign 100 patients to each treatment arm.

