## Results

The study received ethical approval on April 21, 2016, and recruitment began in January 2017. By May 28, 2021, of the proposed 300 participants, 270 (90%) had been randomized, and 244 (81%) had finished the 4-week intervention. Of the proposed 200 participants in the dietary treatment arms who will continue for a 6-month follow-up, 112 (56%) had been on visit 4, and 77 (39%) had been on visit 5.

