#### Secondary Outcome

The secondary outcomes are as follows:

A more conservative cutoff limit in IBS-SSS reduction will be tested, both with a score reduction of ≥100 and ≥50% of the initial IBS-SSS score. Proportions between treatment arms will be compared using chi-square tests.The absolute and percent change in IBS-SSS and GSRS-IBS from randomization visit to the end of intervention period will be analyzed using paired-sample *t* tests within groups and analysis of variance (ANOVA) between groups.Compliance to treatment in relation to treatment outcome will be analyzed using linear regression, with the measure of compliance as the independent variable and IBS-SSS as the dependent variable.Predictors of response to treatment (demographics questionnaire data, microbiota, metabolites, and immunology) will be analyzed using logistic regression, with *responders* and *nonresponders* as the binary outcome variable.Determinants of GI symptoms will be assessed using linear regression, with GSRS-IBS and IBS-SSS as dependent variables.Maintained adherence to dietary intervention will be assessed using food diaries at 3- and 6-month follow-ups, and differences in nutrient intake will be compared between the 2 diets using unpaired-sample *t* tests. Predictors for long-term adherence to diet will be analyzed using logistic regression, with *adherence* and *nonadherence* as binary outcome variables.Changes in extraintestinal symptoms, QoL, work productivity, and psychological factors in relation to treatment will be analyzed using ANOVA for continuous variables and chi-square tests for categorical variables.

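### The no-missing-data statement for the web questionnaires holds only for items within submitted forms, and the plan's dropout allowance and follow-up counts point to whole forms and visits being missed

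*Protocol article*

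**What the plan says.** The Questionnaires section lists eight web-based instruments and says of their platform that "as it will not be possible to skip questions, there will be no missing data". Two of the eight are completed on day 0 only. The other six (anxiety and depression, visceral sensitivity, somatic symptoms, fatigue, work productivity, quality of life) are due on days 0 and 29 and again at 3 and 6 months. The section then sets other instruments apart: "The IBS-SSS, BSF, and GSRS-IBS during the intervention period will be completed using paper questionnaires".

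The Sample Size section expects losses: "To account for a 15% dropout rate, we will assign 100 patients to each treatment arm". The Results section reports that, at May 28, 2021, 270 patients had been randomized and 244 had finished the intervention. Of the 200 planned diet-arm patients, "112 (56%) had been on visit 4, and 77 (39%) had been on visit 5".

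Under Secondary Outcome, "Maintained adherence to dietary intervention will be assessed using food diaries at 3- and 6-month follow-ups". Nutrient intake is compared between the two diets with unpaired t tests, and predictors of adherence are examined by logistic regression. Statistical Methods plans mixed models for changes over several time points during follow-up.

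**The concern.** Forced entry deals with item non-response. It has no effect on a patient who has left the trial, misses a visit or never opens the form. As written, the sentence promises complete data on six secondary scales at three post-baseline times, which the plan's own dropout allowance contradicts.

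Most is at stake in the 6-month follow-up. One specific aim asks how far participants choose to keep their allocated diet, which is a question about everyone allocated to a diet. A study hypothesis links keeping the diet to the size of the symptom reduction. If attendance also depends on benefit or on staying with the diet, the patients who return diaries are a selected group. An unpaired t test at one visit uses only patients with a diary at that visit and ignores the baseline food record that the protocol already collects.

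**Working it through.** **1. The plan's own figures.**
- With response rates of 65% and 40%, 80% power and a pooled-variance two-proportion formula, n per group is 62 at two-sided α = 0.05 and 83 at α = 0.05/3. The stated 83 is therefore reproduced with a three-comparison correction. It is also reproduced at α = 0.025 with a continuity correction.
- Dropout: 83 / (1 − 0.15) = 97.6, so 98, which the plan rounds to 100 per arm.
- Results: 270/300 = 90%, 244/300 = 81%, 112/200 = 56%, 77/200 = 38.5% (given as 39%). The last two use the planned 200 as denominator, not the number due.

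**2. Loss by day 28.** From January 1, 2017 to May 28, 2021 is 52.8 months, and 270/52.8 = 5.11 randomized per month. About 5.11 × 0.92 = 4.7 patients would still be in their 28 days. Loss is then (26 − 4.7)/(270 − 4.7) = 8%. That is below the 15% allowance but not zero.

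**3. Diet patients due, under uniform accrual (an assumption).** Allocation is 1:1:1, so 270 × 2/3 = 180 diet patients randomized and 244 × 2/3 = 163 completers. The actual split is not reported. Visits 4 and 5 fall 3.92 and 6.92 months after randomization.

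| | Due | Seen | Not seen |
|---|---|---|---|
| Visit 4, randomized | 180 × 48.9/52.8 = 167 | 112 (67%) | 33% |
| Visit 4, completers | 163 × 48.9/51.9 = 153 | 112 (73%) | 27% |
| Visit 5, randomized | 180 × 45.9/52.8 = 156 | 77 (49%) | 51% |
| Visit 5, completers | 163 × 45.9/51.9 = 144 | 77 (54%) | 46% |

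Visit 5 comes 3 months after visit 4. Under uniform accrual that explains a gap of about 10 patients (167 − 156). The observed gap is 112 − 77 = 35.

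**4. Back-loaded accrual.** Let f be the share of the 163 diet completers who finished in the last 6 months (about 12% under uniform accrual). Shortfall at visit 5 = 1 − 77/[163(1 − f)].
- f = 20%: 1 − 77/130.4 = 41%
- f = 30%: 1 − 77/114.1 = 33%
- f = 40%: 1 − 77/97.8 = 21%
- Shortfall zero: f = 1 − 77/163 = 53%

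Applied to all 244 completers, f = 40% means about 98 in 6 months (16 per month) against 146 in the preceding 45.9 months (3.2 per month). f = 53% means about 129 (21 per month) against 115 (2.5 per month). The article reports no such surge. The split also matters: with 150 diet completers instead of 163, f = 20% to 40% gives 36% to 14%; with 175 it gives 45% to 27%.

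**5. Consequence for adherence.** If a share s of those due is seen and a of those seen adhere, adherence among all due lies between s·a and s·a + (1 − s). The width is the unseen share, about 21 to 51 percentage points, whatever a is.

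**The case against.** The strongest reply is that the sentence is narrow. It concerns one platform and eight questionnaires, and its stated reason is that questions cannot be skipped, so it can be read as item-level. A reader might infer that it covers the primary outcome. It does not: the IBS-SSS is on paper during the intervention, and the food records are kept in a booklet.

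A reader might also infer that the plan prescribes analyses of attenders only. No section restricts the analysis population, and Statistical Methods already plans mixed models for changes during follow-up, which use all available visits and are valid under missing at random. Rules for a missing primary outcome may stand in the full protocol or SAP, and their absence from an article is no finding.

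Third, the follow-up counts come from an ongoing trial. The number due is not stated, the shortfall rests on an assumed accrual pattern, and late visits cannot be told from missed ones. Counting a missing diary as non-adherence is itself a strong assumption, since patients are free to continue the diet or not, and a missed visit does not show that it was stopped.

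All of this stands and limits the point. Two things remain. Taken literally, the sentence is untrue for forms that are never submitted. And the t tests on nutrient intake and the adherence analyses do depend on returned diaries.

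**Conclusion.** The point holds in a limited form. The statement is correct for items within submitted web forms and wrong for the forms due at day 29 and at 3 and 6 months, and it sits badly with the 15% dropout allowance and the visit counts. The 6-month shortfall among diet patients due is about 46% to 51% under uniform accrual and about 41% to 21% if 20% to 40% of diet completers finished in the last 6 months. All these figures assume that two thirds of patients were on a diet, and none separates missed from late visits. That about half were not seen is one end of this range and not a fact the article reports.

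A reader might go on to infer that adherence and benefit will be overstated. That is plausible, but the documents do not show it: the direction depends on why patients did not attend, which is not reported. The exposure is greatest for nutrient intake and maintained adherence. The primary outcome is not affected by this sentence.

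**What to change.** 1. Limit the sentence to: *no item-level missing data in submitted web forms*.
2. Report attendance at visits 4 and 5 against the number of diet patients due at each visit, separating missed visits from those still outstanding.
3. Replace the unpaired t tests on 3- and 6-month nutrient intake with a mixed model on the baseline, 3- and 6-month food records of all diet-arm patients. This matches the mixed models already planned for follow-up changes. It keeps patients with one follow-up diary, uses the baseline record and is valid under missing at random.
4. Report maintained adherence with a sensitivity analysis that counts patients without a diary as non-adherent. Since that rule can bias adherence downward, it serves as a lower bound and need not replace the main analysis.

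The cost is a change of wording and modest extra analysis, with no new data to collect. The adherence figures may look less favourable.

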#### Biological Samples

Fasting blood samples will be taken and sent to the Department of Clinical Chemistry, Sahlgrenska University Hospital, Gothenburg, Sweden, for analysis of transglutaminase, immunoglobulin A antibodies, total immunoglobulin A levels, hemoglobin, white cell count, platelets, sodium, potassium, creatinine, calcium, C-reactive protein, thyroid-stimulating hormone, free thyroxine, aspartate aminotransferase, alanine aminotransferase, albumin, glucose, hemoglobin A_1c_, and blood lipids (cholesterol, high-density lipoprotein, low-density lipoprotein, and triglycerides) at visit 2. At visits 3, 4, and 5, glucose, hemoglobin A_1c_, and blood lipid levels will be analyzed. At visits 2, 3, 4, and 5, a 4 mL serum sample will be taken and stored at 4 °C for 30 minutes before being centrifuged at 4 °C at 4000 revolutions per minute for 10 minutes, whereby 1 mL serum will be frozen at –80 °C within 2 hours for later analysis of metabolomics as well as for other analyses. Urine samples (3 mL) will be centrifuged at 4 °C at 4000 revolutions per minute for 10 minutes and frozen at –80 °C within 2 hours for later analysis of metabolomics. Serum and fecal and urinary samples will be analyzed with nuclear magnetic resonance and gas chromatography mass spectrometry for metabolomic profiling, and microbial composition and function will be analyzed using whole genome sequencing.

At visits 2 and 3, 3 mL serum and 4 mL heparin plasma will be frozen at –80 °C for later immunological analyses. Biological samples that are not immediately analyzed will be stored at –80 °C in a biobank at our unit.

## Results

The study received ethical approval on April 21, 2016, and recruitment began in January 2017. By May 28, 2021, of the proposed 300 participants, 270 (90%) had been randomized, and 244 (81%) had finished the 4-week intervention. Of the proposed 200 participants in the dietary treatment arms who will continue for a 6-month follow-up, 112 (56%) had been on visit 4, and 77 (39%) had been on visit 5.

### Outcomes

#### Primary Outcome

The primary outcome measure will be the proportion of patients who respond favorably to the treatment regarding the severity of IBS symptoms. Responders will be defined as participants with a score reduction in IBS-SSS ≥50 (ie, calculated as the change in IBS-SSS between randomization visit and end of the intervention period, with a total score ranging from 0 to 500), which is considered a clinically relevant symptom reduction [16], and a cutoff that is commonly recommended for use in clinical studies to define responders.

#### Secondary Outcome

The secondary outcomes are as follows:

A more conservative cutoff limit in IBS-SSS reduction will be tested, both with a score reduction of ≥100 and ≥50% of the initial IBS-SSS score. Proportions between treatment arms will be compared using chi-square tests.The absolute and percent change in IBS-SSS and GSRS-IBS from randomization visit to the end of intervention period will be analyzed using paired-sample *t* tests within groups and analysis of variance (ANOVA) between groups.Compliance to treatment in relation to treatment outcome will be analyzed using linear regression, with the measure of compliance as the independent variable and IBS-SSS as the dependent variable.Predictors of response to treatment (demographics questionnaire data, microbiota, metabolites, and immunology) will be analyzed using logistic regression, with *responders* and *nonresponders* as the binary outcome variable.Determinants of GI symptoms will be assessed using linear regression, with GSRS-IBS and IBS-SSS as dependent variables.Maintained adherence to dietary intervention will be assessed using food diaries at 3- and 6-month follow-ups, and differences in nutrient intake will be compared between the 2 diets using unpaired-sample *t* tests. Predictors for long-term adherence to diet will be analyzed using logistic regression, with *adherence* and *nonadherence* as binary outcome variables.Changes in extraintestinal symptoms, QoL, work productivity, and psychological factors in relation to treatment will be analyzed using ANOVA for continuous variables and chi-square tests for categorical variables.

#### Other Outcomes

Other outcomes are as follows:

Changes in metabolite profiles during intervention and follow-up will be analyzed using orthogonal projections to latent structures discriminant analysis (OPLS-DA) and orthogonal projections to latent structures with effect projection (OPLS-EP).Changes in microbiota composition during intervention and follow-up will be analyzed using OPLS-DA and OPLS-EP.Changes in immunological markers during the intervention will be analyzed using OPLS-DA and OPLS-EP.Patients’ subjective experiences related to the dietary intervention will be described by qualitative methods, using inductive content analysis.

### Measure of Compliance

During the intervention period, patients receiving dietary treatment should note any deviations from their allocated diet in a daily symptom diary. In addition to the recipes and foods that follow each intervention, there will be specified lists of foods that will be allowed and forbidden during the intervention period. As long as a study participant complies with the foods that are on the *allowed* list and the framework of the dietary regime, the participant will be considered compliant. The compliance will be calculated for each week. Any deviation that does not adhere to the intervention diet will result in a score reduction (at most –1 for each deviation). Compliance with medical treatment will be examined during telephone check-ups and at visit 3 but will not be scored.

### Statistical Methods

Normally distributed variables will be presented as mean (SD) and nonnormally distributed variables as median (range). Differences in means between the 3 intervention groups will be analyzed with ANOVA, using Bonferroni corrections for multiple testing. For the main outcome, that is, to compare the proportion of responders in each treatment group, chi-square tests will be applied. For absolute change in IBS-SSS, the percentage change will be calculated and analyzed with paired *t* tests within groups (baseline vs end of intervention) and using ANOVA for comparisons between groups. The proportion of patients with ≥50% decrease in IBS-SSS will be compared using chi-square test between the groups. For comparing the changes at multiple time points (during follow-up), mixed model analyses will be used.

Logistic regression will be applied to evaluate predictors of response for the various treatments (binary outcome responders or nonresponders), and the determinants of GI symptoms (IBS-SSS, as a continuous variable) will be assessed using bivariate and multivariable linear regression analyses. Furthermore, multivariate analyses and bioinformatics will be applied to metabolomics, microbiota, and immunological markers.

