### Participant Timeline

The study comprises a 10-day screening period, followed by a 4-week intervention and a 6-month follow-up period. An overview of the enrollment, allocation, and intervention process is shown in Figure 1.

In short, at the first visit, after receiving verbal and written information about the study, all patients will provide their written informed consent. The diagnosis of IBS will be confirmed by a physician, who will perform a physical examination and ensure that the patients fulfill the Rome IV criteria for IBS [1]. Thereafter, a 10-day screening period will begin, where a daily stool diary based on the Bristol stool form (BSF) scale [17] will be completed, and a 4-day food record will be kept. On their return visit, the patients will complete the IBS-SSS to assess the severity of their IBS symptoms during the 10-day screening period. Patients who score ≥175 on the IBS-SSS (ie, moderate to severe IBS symptoms) will be eligible to be randomized into one of the treatment arms. Patients with an IBS-SSS score <175 will be excluded from further participation and will be offered a regular visit to a dietitian or physician at the clinic.

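### The primary responder comparison is an unadjusted chi-square; adding baseline IBS-SSS, already held for every randomised patient, would gain a few points of power at almost no cost

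*Protocol article*

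**What the plan says.** - **Primary test** (Statistical Methods): "For the main outcome, that is, to compare the proportion of responders in each treatment group, chi-square tests will be applied". No covariate is named. Logistic regression of responder status is planned in the same section, but only to look for predictors of response.
- **Endpoint** (Primary Outcome): a fall in IBS-SSS of at least 50, "calculated as the change in IBS-SSS between randomization visit and end of the intervention period".
- **Baseline score** (Questionnaires): the IBS-SSS "will be filled in at day -1, day 7, day 14, day 21, day 28, and 3 and 6 months after completion of the intervention". It also decides entry (Participant Timeline): "Patients who score ≥175 on the IBS-SSS (ie, moderate to severe IBS symptoms) will be eligible to be randomized into one of the treatment arms". So every randomised patient has one.
- **Allocation**: "No stratification will be made before randomization".
- **Sample size**: "the expected response rate is set to 40% (LCD), 65% (LFTD), and 40% (OMT) in the treatment arms", with alpha .05, 80% power, 83 per group, and 100 assigned per arm to allow for 15% dropout.
- **Specific Aims**: baseline symptom severity is listed among the pretreatment factors that might predict response.

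**The concern.** The same 50-point fall is asked of a patient entering at 175 and of one entering at 450. A fall measured from a noisy score, in patients selected for a high value of that score, will usually be larger where the baseline is higher, partly through regression to the mean. Baseline IBS-SSS is therefore a likely predictor of the primary endpoint, and the article itself treats it as a candidate. The primary test does not use it, and unstratified allocation does not balance it by design.

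At stake is precision. Prognostic variation stays in the error term, and any chance difference in baseline severity between arms stays in the estimated difference in responders. The point concerns the binary primary endpoint only, not the ANOVA of change scores.

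**Working it through.** **1. The plan's own figure.** For two proportions, two-sided and without continuity correction:

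n = [z(1−α/2)·√(2p̄q̄) + z(0.80)·√(p₁q₁ + p₂q₂)]² / (p₁ − p₂)²

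With p₁ = 0.40, p₂ = 0.65 and p̄ = 0.525, √(2p̄q̄) = √0.49875 = 0.706 and √(0.24 + 0.2275) = 0.684.

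- α = .05: (1.960×0.706 + 0.842×0.684)²/0.0625 = 61.4, so 62 per group (70 with continuity correction).
- α = .05/3: (2.394×0.706 + 0.842×0.684)²/0.0625 = 82.2, so **83** per group.
- α = .05/2 with continuity correction also gives 83.
- Dropout: 83/0.85 = 97.6, so 98, which the article rounds to 100.

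The stated 83 is thus an unadjusted calculation at a split alpha that the article does not state. With 83 per group, crude power for one contrast is 80.5% at .05/3 and 90.4% at .05. Both levels are carried below.

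**2. When baseline predicts the fall.** Let B be baseline, F the end score and β the slope of F on B. Then Cov(B, B − F) = (1 − β)·Var(B). This is zero only if β = 1.

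**3. How strongly.** With r the baseline-to-end correlation and k = SD(F)/SD(B):

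rho = (1 − rk)/√(1 + k² − 2rk)

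The article gives neither r nor k, so these are assumptions:

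| r | k | rho |
|---|---|---|
| 0.5 | 1.0 | 0.50 |
| 0.5 | 1.2 | 0.36 |
| 0.5 | 1.4 | 0.24 |
| 0.5 | 1.5 | 0.19 |
| 0.6 | 1.2 | 0.28 |

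The 175 cut-off narrows the spread of B but not of F, which pushes k above 1 and rho below 0.5.

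**4. Power for one contrast.** Simulation with 6,000 trials per setting, 83 per arm, 40% v 65%, and baseline assumed N(300, 75) truncated to 175–500. The crude two-proportion test is compared with the likelihood-ratio test for arm in a logistic model containing baseline.

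| rho | α .05: crude → adjusted | α .05/3: crude → adjusted |
|---|---|---|
| 0 | 91.0 → 90.8% | 80.4 → 80.9% |
| 0.2 | 90.7 → 91.1% | 80.6 → 81.9% |
| 0.3 | 90.9 → 92.1% | 80.2 → 83.1% |
| 0.4 | 90.2 → 93.3% | 80.2 → 85.0% |
| 0.5 | 90.5 → 94.7% | 80.1 → 88.0% |

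Monte Carlo standard error is at most about √(0.8×0.2/6000) = 0.5 point. The difference at rho 0, α .05 is within that error. A Wald test of the arm coefficient, also with truncated baseline, gives slightly smaller gains: about 0–1 point at rho 0.2, 3 at about 0.35, and 4–7 at 0.5 across the two alpha levels.

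**5. Power for LFTD beating both arms, α .05 each.** Simulation with 4,000 trials per setting, untruncated normal baseline, and the standardised risk difference from a three-arm logistic model: rho 0.2, 84.4 → 85.6%; 0.3, 85.2 → 87.1%; 0.4, 84.1 → 87.9%; 0.5, 84.1 → 90.6%. With truncation and the Wald test the gains are about 0–1 point at 0.2, 2–4 at 0.3–0.4 and 7 at 0.5, from a crude 83–84%.

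**6. Type I error.** With no true difference, at α .05 and rho 0.3 and 0.5, rejection was 4.5–4.7% crude and 4.9–5.3% adjusted.

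**7. Chance imbalance.** With 83 per arm, the difference in mean baseline between two arms has a standard error of √(2/83) = 0.155 baseline SD. The chi-square allows for this in its error rate but does not remove it from the estimate.

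**The case against.** The strongest reply is that nothing here is an error, and that stands. A chi-square on a randomised binary endpoint is valid, its type I error already covers chance imbalance, and the sample size was set on unadjusted proportions, so test and sample size agree. Baseline severity will also be examined as a predictor of response, though not in the comparison of arms.

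Three stronger readings are tempting, and the article does not support them.

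- **Unstratified allocation biases the primary result.** It does not. Randomisation protects the comparison on average, and only precision is affected.
- **Adjustment lifts power from 69% to 80%.** That figure needs rho = 0.5, and it requires LFTD to beat both arms with each tested at .05/3. The .05/3 level is only inferred: the article states .05, and attaches Bonferroni to the ANOVA of means. If both contrasts must be won, each can be tested at the full .05, and crude power is then already 83–84%.
- **Rho is 0.5.** This follows only if baseline and end SDs are equal and their correlation is 0.5. The entry cut-off makes equal SDs doubtful.

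The reply also notes that a published primary analysis would change late, with 270 of 300 patients randomised by May 2021 and one arm open label. That is a real cost. It is reduced because data entry and analysis are done by people blinded to group.

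**Conclusion.** The point holds as a matter of efficiency. The primary test leaves out a baseline score from which the endpoint is computed and which every randomised patient has. The likely gain from using it ranges from negligible (rho about 0.2) to a few points (rho 0.3 to 0.4), and reaches about 7 points only near rho 0.5. Beyond simulation error, no setting with 83 per arm showed a loss of power.

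This rests on the article's 40/65/40% response rates and on assumed values for rho and the baseline distribution, none of which can be checked from the document. The direction does not depend on those values, unless the slope of end score on baseline is exactly 1, in which case the gain is nil. The chi-square result would remain interpretable if nothing were changed.

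**What to change.** In Statistical Methods, replace the primary chi-square with a logistic regression of responder status on treatment arm and continuous baseline IBS-SSS from the randomisation visit. Report LFTD minus LCD and LFTD minus OMT as standardised differences in responder proportion (average the model's predictions over all patients under each arm, with a robust or delta-method standard error). Keep the unadjusted chi-square as a supportive analysis. Record the change, with its date, before the analysts are unblinded.

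Cost: one sentence in the plan and a few lines of code, with no new data or patients. The downside is small: a published primary analysis changes late in recruitment, and the main result comes from a model rather than a contingency table. The retained chi-square and the blinded analysts mitigate both.

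### The only analysis specified for predictors of treatment response uses the 50-point responder cut of IBS-SSS; a baseline-adjusted continuous model beside it would recover discarded information at almost no cost

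*Protocol article*

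**What the plan says.** The Secondary Outcome section lists the candidates ("Predictors of response to treatment (demographics questionnaire data, microbiota, metabolites, and immunology") and says that they "will be analyzed using logistic regression, with *responders* and *nonresponders* as the binary outcome variable". Statistical Methods repeats the choice: "Logistic regression will be applied to evaluate predictors of response for the various treatments (binary outcome responders or nonresponders"). The Primary Outcome section supplies the cut: "Responders will be defined as participants with a score reduction in IBS-SSS ≥50", measured from the randomization visit to the end of the intervention.

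Elsewhere the same score is kept continuous:

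- **Arm comparisons.** "The absolute and percent change in IBS-SSS and GSRS-IBS from randomization visit to the end of intervention period" is analysed with paired t tests and ANOVA.
- **Determinants of symptoms.** In the same sentence of Statistical Methods as the logistic regression, "the determinants of GI symptoms (IBS-SSS, as a continuous variable) will be assessed using bivariate and multivariable linear regression analyses".
- **Compliance.** IBS-SSS is regressed on a compliance measure (Secondary Outcome).

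Finding pretreatment factors that predict response is one of the Specific Aims. It is also the fifth secondary hypothesis, and the abstract's Conclusions and the Discussion both present it as an expected gain from the trial.

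**The concern.** The Primary Outcome section justifies the 50-point cut as clinically relevant and commonly recommended for defining responders. That is a sound reason for comparing proportions between arms. It is a weaker reason for making the cut the only named outcome in a search for associations. In that search a 49-point fall is coded the same as a worsening, and a 51-point fall the same as a 300-point fall.

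The candidate list is long and the arms were sized for the primary comparison. If about two fifths of the information in the outcome is set aside, true predictors are more likely to be missed, although the data that could show them are already collected. The primary result is not at stake. What is at stake is the yield of a stated aim.

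**Working it through.** **Inputs from the protocol (Sample Size).** For the primary outcome, "the expected response rate is set to 40% (LCD), 65% (LFTD), and 40% (OMT) in the treatment arms". The stated requirement is 83 per group at 80% power and α = .05. Dropout is 15%, with 100 assigned per arm.

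**Step 1: reproduce the plan's figure.** For 65% versus 40% the mean is 0.525. With pooled variance under the null, n = [z(α)·√(2 × 0.525 × 0.475) + z(0.80)·√(0.40 × 0.60 + 0.65 × 0.35)]² / 0.25². With two-sided α = .05/3, z(α) = 2.394, so n = (2.394 × 0.7062 + 0.8416 × 0.6837)² / 0.0625 = 82.2, rounded up to 83. The figure is reproduced. (Two-sided .05/2 with continuity correction also gives 83; unadjusted two-sided .05 gives 62.) For dropout, 83/0.85 = 97.6, so 98, and the plan assigns 100. Expected evaluable patients per arm are 100 × 0.85 = 85. Hence the range of 83 to 85.

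**Step 2: information kept by the cut.** If the change is normal and a share p are responders, a binary analysis keeps φ(z_p)² / [p(1 − p)] of the information in the continuous one.

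- p = 0.40: 0.3863² / 0.24 = 0.622
- p = 0.65: 0.3704² / 0.2275 = 0.603

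So 83 patients carry the information of 83 × 0.603 = 50 to 83 × 0.622 = 52. This step needs normality but no assumed correlation.

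**Step 3: power by formula.** If the continuous analysis has 80% power at two-sided .05, its noncentrality is 1.960 + 0.842 = 2.802. The binary analysis has Φ(2.802·√0.622 − 1.960) = Φ(0.25) = 60% at 40% responders, and Φ(2.802·√0.603 − 1.960) = Φ(0.22) = 59% at 65%.

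**Step 4: power by simulation.** Settings: n = 83, one standardised predictor, bivariate normal with the change score, 2000 runs per setting, two-sided .05. Linear regression on the change is compared with logistic regression on the cut.

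| Assumed r | Linear / logistic, 40% responders | Linear / logistic, 65% responders | Loss (points) |
|---|---|---|---|
| 0.15 | 28% / 18% | 26% / 16% | 10–11 |
| 0.20 | 43% / 29% | 45% / 28% | 14–17 |
| 0.25 | 64% / 43% | 64% / 40% | 22–24 |
| 0.30 | 80% / 58% | 81% / 55% | 22–25 |
| 0.35 | 91% / 74% | 91% / 71% | 17–20 |
| 0.40 | 97% / 82% | 96% / 81% | 15 |

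Moving from 83 to 85 patients changes this very little.

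**Step 5: does this carry over to the proposed model?** The table uses the unadjusted change score. For any predictor other than baseline itself, regressing day-28 score on predictor and baseline gives the same predictor coefficient, apart from sign, as regressing the reduction on the same two terms. A further simulation, with the predictor independent of baseline, gave the adjusted model essentially the same power as the change-score model when baseline was unrelated to the change, and more when it was related. The table is therefore not flattering to the proposal under that condition.

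**The case against.** **The analysis fits the aim.** The Specific Aims define response as a reduction of at least 50 points and then ask what predicts response. For personalising treatment, the chance of responding is a natural quantity, and a factor that shifts the mean need not be one that moves patients across the threshold. This stands. It is why the logistic model should be kept and not demoted.

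**Continuous regressions are already planned.** A reader might infer that the plan never relates IBS-SSS as a continuous score to patient factors. The text does not support that: the determinants analysis does so, and multivariate analyses are planned for the metabolomic, microbiota and immunological data. But the determinants item is listed separately and names neither change nor baseline adjustment. The multivariate sentence names no outcome, and the methods under Other Outcomes address changes in the markers themselves. None is specified as an analysis of response. A condensed article may leave such detail to a fuller document. The choice of a binary outcome for predictors of response, however, is stated twice.

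**The power loss is conditional.** A reader might infer a flat cost of about 20 points. The protocol gives no predictor effect size and no SD of the change, and the loss falls to 10 to 15 points at either end of the range. The score is bounded and entry requires at least 175, so normality is approximate. The calculation also tests one predictor at unadjusted .05, whereas the search covers many. All of this stands, and a range is the honest statement.

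**By-arm models are an inference.** The wording about the various treatments suggests separate models but does not exclude pooled ones. In a simulation with 249 patients (3 × 83), the loss was about 11 points at r = 0.10 and 19 to 23 points at r = 0.15 to 0.20. Pooling moves the problem to weaker predictors and does not remove it.

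**Conclusion.** The concern holds in a limited form. For predictors of response, the protocol specifies only a logistic regression on the 50-point cut. Under an approximately normal change score, that keeps about 60% to 62% of the information at the plan's response rates. By arm, with 83 to 85 evaluable patients and one predictor at two-sided .05, power falls by roughly 10 to 25 points for assumed correlations of 0.15 to 0.4, most near 0.3.

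The documents do not support calling the logistic regression invalid or contradictory. The between-arm comparisons are untouched. This is a stated choice for a secondary aim that has a better companion available at little cost.

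**What to change.** For each candidate predictor, prespecify a linear regression of day-28 IBS-SSS on the predictor with baseline IBS-SSS as covariate. Report it alongside the 50-point responder logistic regression, which is retained to give responder odds. Leave the primary outcome and the responder definition unchanged.

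Baseline severity is itself a candidate predictor, so its coefficient needs separate reading. If day-28 score = a + b × baseline, then reduction = −a + (1 − b) × baseline. Report 1 − b, the change-scale coefficient, rather than b.

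The cost is some wording, one more set of model runs and a second scale to report. No new data are needed.
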